## Abstract

**Background:**

This study aims to evaluate the feasibility and efficacy of a complex health intervention, based on the combination of conventional Western medicine and traditional Chinese medicine (TCM), in an outpatient department of a university hospital for patients with frequent episodic or chronic tension-type headaches.

**Methods/design:**

This is a prospective randomized controlled pilot study with four balanced treatment arms (usual care, acupuncture, training, and training plus acupuncture). Each arm will have 24 patients. After the initial screening examination and randomization, a 6-week treatment period follows, with treatment frequencies decreasing at 2-week intervals. After completion of the intervention, two follow-up evaluations will be performed 3 and 6 months after the start of treatment. At predefined times, the various outcomes (pain intensity, health-related quality of life, pain duration, autonomic regulation, and heart rate variability) as well as the participants’ acceptance of the complex treatment will be evaluated with valid assessment instruments (Migraine Disability Assessment, PHQ-D, GAD-7, and SF-12) and a headache diary. The acupuncture treatment will be based on the rules of TCM, comprising a standardized combination of acupuncture points and additional points selected according to individual pain localization. The training therapy comprises a combination of strength training, endurance training, and training to improve flexibility and coordination. Besides descriptive analyses of the samples, their comparability will be assessed using an analysis of variance (ANOVA) or chi-squared tests. Analyses will be performed on an intention-to-treat basis. Potential interaction effects will be calculated using a repeated-measures ANOVA to test the primary and secondary hypotheses. In supplementary analyses, the proportion of treatment responders (those with a 50% reduction in the frequency of pain episodes) will be determined for each treatment arm.

**Discussion:**

This trial may provide evidence for the additive effects of acupuncture and medical training therapy as a combination treatment and may scientifically support the implementation of this complex health intervention.

**Trial registration:**

Registered on 11 Feburary 2019. German Clinical Trials Register, DRKS00016723.

## Background

Both acupuncture and medical training therapy (MTT) are used as monotherapies to treat tension-type headaches. The usefulness of both acupuncture and MTT as effective treatment options with moderate but clinically relevant effect sizes has been demonstrated in meta-analyses [1, 2]. The benefits of acupuncture treatment have been shown in studies comparing acupuncture with usual care [3, 4] and so-called sham acupuncture [5]. For MTT, significant reductions in the frequency of headache attacks [6] and in analgesic consumption [7] have been demonstrated in patients with tension-type headaches. Compared with acupuncture, MTT has been shown to significantly improve quality of life and patient satisfaction [8, 9]. Despite the evidence in support of the effectiveness of acupuncture and MTT, we could not identify any studies evaluating the efficacy of a combination of acupuncture and MTT for tension-type headaches in comparison with the two treatment modalities alone or with usual care.

Tension-type headaches are common. They have a significant socioeconomic impact, primarily due to disease-associated incapacity for work and medical treatment costs [10, 11]. Whether complementary combination therapies are more effective than each treatment modality alone is of clinical relevance and has not yet been answered. In this study, acupuncture as a treatment modality in traditional Chinese medicine (TCM) is combined with MTT, a classical Western medical treatment.

In addition to the classical outcomes of headache studies, which will be used to evaluate the efficacy of the two methods regarding pain, analgesic consumption, anxiety, and depression, this study will also address whether the two therapies affect individual psychological stress levels, as an association between increased stress levels and tension-type headaches has been reported. Several studies assessing techniques involving physical contact, such as Thai massage, showed positive changes in heart rate variability (HRV), which is used as an objective measure of psychological stress.

In addition, the study will assess whether those participating in the study have a functional disorder of the chewing system (temporomandibular disorder or TMD). Speciali and Dach [12] considered several epidemiological studies in a systematic review, which showed the co-occurrence of TMD and tension-type headaches. Moreover, published studies have shown improvements in headaches when a co-existing TMD was treated with dental interventions alone [13].

By involving experts in TCM, the proposed study may provide information about another interesting aspect, which is that tension-type headaches are described as a mild to moderate, holocranial headaches with a dull, pressing character [14]. However, differences in the location of maximum pain have no impact on treatment decisions based on the International Classification of Headache Disorders (3rd Edition) [15] of the International Headache Society (IHS). By contrast, the acupuncture points to be used for treatment are selected according to the meridian diagnosis of TCM, which is primarily guided by where the pain is located and where it radiates to. Independent of investigating whether selecting acupuncture points according to TCM criteria is superior to the unspecific effect of random needling, the proposed study will investigate the inter-rater reliability of meridian diagnosis. Moreover, the subjective diagnosis of a TCM specialist with an assignment to corresponding meridians will be compared with the patient-created pain mapping with an assignment to local meridians. However, this study will not compare acupuncture with random acupuncture because this would tend to underestimate the effects of acupuncture [16]. As mentioned in the conclusion of the meta-analysis by Linde et al. [1], a non-inert effective therapy (i.e., MTT) will be compared with acupuncture and usual care.

### Research questions

Primary null hypothesis:
For the primary endpoint, (1) acupuncture and MTT, alone or in combination, are not superior to usual care according to IHS criteria, and (2) the combination of the two non-pharmacological treatment modalities is not superior to either treatment modality alone.

Secondary null hypotheses:
None of the treatment modalities improves HRV as a measure of individual psychological stress in headache patients.None of the treatment modalities reduces the occurrence of tension-type headaches (days per month), the duration of pain episodes, or the consumption of analgesics by individuals.None of the treatment modalities influences health-related quality of life, physical and mental fitness, or psychological health.TMD as a comorbidity has no impact on treatment outcomes for tension-type headaches in the study setting.Kappa as a measure of inter-rater reliability of Chinese meridian diagnosis is <0.5 in comparisons.

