### Sample size estimation

The sample size calculation was based on the results of Endres et al. [17]. The study was powered to detect a small interaction effect of time × intervention dose (*f* = 0.15) for the primary endpoint (α = 0.05) with a power of 80% in a variance analysis with five repeat measurements and four study groups. With these targets, 20 patients per study group were required for analysis. Assuming a dropout rate of 20% over the course of the trial, 24 patients must be included in each study group; thus, recruitment of 96 participants is required. The sample size calculation was performed using the G*Power 3 software.

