### Statistical analysis

Descriptive statistics will be used to describe the study population. The comparability of the study groups regarding age, gender, and outcome characteristics will be determined using an analysis of variation (ANOVA) or chi-squared tests. A significance level of *p* < 0.05 will be used for all tests. Analyses will be performed on an intention-to-treat basis. Multiple imputation will be used to handle missing data. To test the primary hypothesis, potential interaction effects (time × intervention) with pain as the primary endpoint will be calculated using a repeated-measures ANOVA. Supplementary Bonferroni-corrected post hoc tests will assess potential intragroup effects. Secondary interval-scale outcome measures will be analyzed using the same strategy. The proportion of treatment responders (those with at least a 50% reduction in the frequency of pain episodes) will be determined in supplementary analyses for the various treatment arms.

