## Discussion

We expect to find positive treatment effects in all intervention groups for all outcomes in comparison with the usual care or control group. Furthermore, we expect to demonstrate the additive effects of acupuncture and MTT as a combination treatment and to provide scientific evidence to support the implementation of this complex health intervention. Since the two interventions differ in their mechanisms of action, consequently they exert analgesic, autonomic, and psychological effects at different levels. Thus, we expect different effects for each group for pain, the primary endpoint, and for the various secondary endpoints, such as mood, psychological stress, quality of life, and frequency of pain episodes. In addition, we believe that analyzing the correlations between the various outcome parameters with the applied treatment will provide information about the levels at which the effects occur. Furthermore, the influence of temporomandibular disorder on treatment effects will be a basic component of the data analysis. Figure 3 shows how the outcomes are related to each other. An evaluation of adverse events and their severity are important for safety and for patient acceptance of the treatment. Finally, these treatment modalities will be rated by the participating patients with regard to content and time requirements.

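### Primary null (2) can be read as refuted when the combination beats only one modality, and the named analysis does not settle whether it must beat one or both

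*Protocol article*

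**What the plan says.** The protocol article addresses the combination claim in five places.

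- **Research questions**, primary null, part (2): "the combination of the two non-pharmacological treatment modalities is not superior to either treatment modality alone".
- **Background**, the question behind it: "Whether complementary combination therapies are more effective than each treatment modality alone is of clinical relevance and has not yet been answered".
- **Discussion**, the intended use: "we expect to demonstrate the additive effects of acupuncture and MTT as a combination treatment and to provide scientific evidence to support the implementation".
- **Statistical analysis**, the test of the primary hypothesis: "potential interaction effects (time × intervention) with pain as the primary endpoint will be calculated using a repeated-measures ANOVA". The only follow-up tests named are these: "Supplementary Bonferroni-corrected post hoc tests will assess potential intragroup effects". A level of 0.05 applies to all tests; whether it is one- or two-sided is not stated.
- **Sample size estimation**: "The study was powered to detect a small interaction effect of time × intervention dose", with f = 0.15, alpha 0.05, 80% power, four groups and five measurements, giving 20 analysed per group.

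The primary endpoint (Primary outcome) is the change in mean pain intensity from T1 to T3. The article names no contrast of the combination with acupuncture or with medical training therapy (MTT). It also does not say whether one or both of these must be significant to reject null (2).

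**The concern.** Write A, M and C for the mean improvement under acupuncture, MTT and the combination.

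- *Superior to neither*: the null is C ≤ A **and** C ≤ M. It is false as soon as C exceeds one of the two.
- *Not superior to each*: the null is C ≤ A **or** C ≤ M. It is false only when C exceeds both.

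The wording of null (2) ordinarily means the first. The Background question needs the second. The two lead to opposite decisions in the case that matters most for a combination: one component works, the other adds nothing, and C merely equals the better single treatment. The first null is then false and the second is true.

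Null (2) carries the trial's novel claim and the case for the more burdensome arm, in which every training session is followed by acupuncture. If the choice between one contrast and both stays open until the data are seen, the claim can rest on the easier comparison.

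**Working it through.** **1. The plan's own figure.** G*Power's within-between interaction uses λ = f²·N·m/(1 − ρ), df1 = (k − 1)(m − 1), df2 = (N − k)(m − 1). The article gives f = 0.15, k = 4, m = 5 and N = 80. It does not give ρ or the sphericity correction; I assumed the program defaults, ρ = 0.5 and ε = 1.

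λ = 0.0225 × 80 × 5 / 0.5 = 18.0; df1 = 12; df2 = 304; power = 0.802.

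The stated 20 per group is reproduced. This is power for the overall interaction, not for C versus A or C versus M.

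**2. What the overall test can show.** For the T1–T3 change, the time × intervention test is a one-way test on change scores. Assume a change-score SD of 1, 20 per arm, usual care 0, and all three active arms at 0.7, so that combining adds nothing.

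λ = n·Σ(μ − mean)² = 20 × 0.7² × 3/4 = 7.35; df 3 and 76; power = 0.588.

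About 59% of such trials give a significant interaction driven only by active treatment against usual care. The named post hoc tests look within groups, so they cannot correct this.

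**3. One contrast or both.** I simulated change scores with SD 1, 20 per arm, two-sample t-tests at two-sided 0.05, counting success only in favour of the combination. In every row C = A, so MTT adds nothing. The effects in SD units are assumptions, because the article gives no SD or arm means.

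| A, M, C (SD) | Gap A − M | At least one succeeds | At least one, Bonferroni for two | Both succeed |
|---|---|---|---|---|
| 0.7, 0.7, 0.7 | 0 | 5% | 2% | 0.5% |
| 0.7, 0.5, 0.7 | 0.2 | 10% | 6% | 1% |
| 0.5, 0, 0.5 | 0.5 | 34% | 24% | 2% |
| 0.7, 0, 0.7 | 0.7 | 58% | 46% | 2.4% |

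The last column cannot exceed 2.5%: C = A, and a two-sided 0.05 test favours the combination wrongly at most 2.5% of the time. Bonferroni does not cure the third column, because the difference from the weaker arm is real.

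**4. Power of the stricter rule when effects truly add up.**

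| A, M, C (SD) | n per arm | At least one | Both |
|---|---|---|---|
| 0.7, 0.7, 1.4 | 20 | 74% | 42% |
| 0.7, 0.7, 1.4 | 24 | 81% | 51% |
| 0.5, 0.5, 1.0 | 20 | 49% | 19% |
| 0.5, 0.5, 1.0 | 24 | 56% | 24% |

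For 80% power on both contrasts, about 79 per arm are needed when C exceeds each modality by 0.5 SD, and about 32 per arm at 0.8 SD.

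**The case against.** The strongest reply is that the wording has a second reading. *Not superior to either* can be the negation of *superior to either one*, meaning each, which is the correct null. The Background's use of *each* may then clarify the intent rather than contradict it. This stands as far as it goes: the wording is ambiguous and not plainly an at-least-one rule. But nothing in the analysis section adopts the stricter reading, and a primary null open to two opposite decision rules is badly fixed.

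A reader might infer that the plan commits the trial to declaring a useless add-on superior. The document does not support that. It contains no rule that one significant contrast suffices; the rates in the at-least-one column belong to an assumed rule. The combination *could* be so reported; it cannot be said that it *would* be. A careful author would also name which modality was beaten.

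The large-gap scenarios give MTT no effect, while the Background describes both modalities as effective with moderate effect sizes. That is fair, and it is why the smaller gaps are shown: with similar modalities the excess is slight.

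A success rule is often left to an analysis plan, which is not at hand. Its absence alone would be no finding. The point is that the article words the null loosely and attaches to it a test that answers neither reading.

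Finally, the stricter rule costs power in what the Abstract calls a pilot study. That is true and should be stated.

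**Conclusion.** The point holds as an ambiguity in a primary hypothesis that the named analysis leaves open. On either reading, the four-arm interaction with intragroup follow-up cannot support a claim that the combination beats each single modality.

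The size depends on how far apart the modalities are. With 20 per arm and an at-least-one rule, a combination with one useless component is called superior in about 5% of trials at no gap, rising to 58% at 0.7 SD, against at most 2.5% if both contrasts must succeed. These figures rest on assumed SD-unit effects, equal variances and two-sided 0.05 testing.

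Two limits apply. Beating each modality is not the same as additivity, which the Discussion expects to show ("we expect to demonstrate the additive effects of acupuncture and MTT as a combination treatment"); a clearly sub-additive combination can beat both. And the stated 80% power does not carry over to this claim.

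**What to change.** 1. Reword null (2): the combination is not superior to at least one of the two modalities alone.
2. Name its test: two contrasts on the T1–T3 change in pain intensity, combination versus acupuncture and combination versus MTT.
3. Claim superiority of the combination only if both are significant at two-sided 0.05 in its favour. As an intersection-union test this needs no split of alpha within null (2).
4. If only one succeeds, report superiority to that modality by name and make no general claim for the combination.
5. State that success shows superiority to each modality, not additivity, and that the 80% in Sample size estimation refers to the overall interaction only.

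The change uses data already planned and needs no extra visits or patients. Recruitment is reported as complete, so the sample cannot be assumed to grow. The price is a lower chance of making the claim at 20 per arm: 42% instead of 74% for additive 0.7 SD effects, and 19% instead of 49% for 0.5 SD. The report should say so, so that failure on one contrast is not taken as evidence of no benefit.

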## Methods/design

### Study design

The proposed study is a randomized controlled prospective trial with four balanced treatment arms. It will compare the efficacy of two distinct non-pharmacological treatment modalities (acupuncture vs. MTT), as monotherapies and in combination, with usual care according to IHS criteria for the treatment of common episodic and chronic tension-type headaches. Usual care is the control modality. Subjects will be assigned to one of the four treatment arms (usual care, acupuncture, MTT, and MTT plus acupuncture), using pre-generated randomization lists in a ratio of 1:1:1:1 with varying permutation block sizes. The randomization scheme was prepared by a scientific colleague who is not involved in scheduling, treatment, or evaluation. After the randomization list had been created, written allocation sheets were delivered to the treating physicians in sealed opaque envelopes.

The study is headed by the first and last authors as well as the head of the Departement of Rehabilitation medicine of the Hannover Medical School (CG). Protocol decisions were made in a peer process involving all co-authors. Changes to the study protocol can be made only with the written consent of the ethics committee.

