### Patient recruitment

Patients will be invited to participate in the research study by notices in local and regional media and by calls for participation to staff members and students at the Hannover Medical School. Semi-structured telephone interviews and subsequent physical examinations will be performed to select patients with frequent episodic or chronic tension-type headaches according to the diagnostic criteria of the International Classification of Headache Disorders, 3rd Edition (IHS 2.2 and IHS 2.3).

After the telephone screening by two scientific assistants, a potential participant is registered and given an initial appointment, which includes a preliminary medical examination, checking of the inclusion and exclusion criteria, collecting comprehensive information, and providing consent to participate. After this appointment and consent to participate in the study, the subject draws one of the previously created opaque randomization envelopes, is assigned to the corresponding group, and is given dates for appointments for the intervention and for follow-up appointments. The appointments and schedules of the patients enrolled in the study are generated by a study nurse who is neither involved in the treatment nor in the randomization. Randomization will be overseen by one of the trial directors.

The total study period for each participant will be 7 months (Figs. 1 and 2). This period includes a 4-week baseline period, a 6-week intervention period, and a 20-week follow-up period. During the intervention period, the subjects in the trial groups will receive a total of 12 treatment units in decreasing frequency (three units per week during the first 2 weeks, two units per week during the third and fourth weeks, and one unit per week during the last 2 weeks). During the entire study period, as-needed analgesics (e.g. ibuprofen, aspirin, and paracetamol) can be taken as usual and will be documented in a headache diary.

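### The primary T1–T3 comparison names no baseline covariate, so with 20–24 patients per arm it loses precision and leaves a chance imbalance in headache type uncorrected

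*Protocol article*

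**What the plan says.** - **Population.** Under Patient recruitment, telephone interviews and physical examinations serve "to select patients with frequent episodic or chronic tension-type headaches". Type is thus known before the patient draws an envelope.
- **Allocation.** Under Study design, the lists are pre-generated "in a ratio of 1:1:1:1 with varying permutation block sizes". No stratification factor is named.
- **Size.** Under Sample size estimation, "20 patients per study group were required for analysis"; after the dropout allowance, "24 patients must be included in each study group; thus, recruitment of 96 participants is required".
- **Primary endpoint.** Under Primary outcome, it is each patient's change in mean pain intensity from T1 (before treatment) to T3 (six weeks after treatment ends).
- **Primary test.** Under Statistical analysis, the time × intervention effects "will be calculated using a repeated-measures ANOVA". No covariate is named. Baseline differences are handled only by testing whether the arms are comparable in age, gender and outcome characteristics. Headache type is not listed.
- **Background care.** Under Control group, continued prophylaxis is mentioned only for chronic headache.

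**The concern.** Headache type defines the population, is recorded for everyone, and in the control group bears on which background treatment may continue. In arms of 20 to 24 it can easily be distributed unevenly. A comparability test does not correct an imbalance; it only reports one.

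The stated model also makes no use of T1 pain beyond subtracting it. An unadjusted change score is less precise than a comparison of T3 pain adjusted for T1 pain whenever the two are less than perfectly correlated (with equal spread at both times). In a trial this small, both omissions cost power. The type omission also leaves the reader of an uneven result unable to separate treatment from case mix.

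**Working it through.** **1. The plan's own sample size.** Stated inputs: f = 0.15, α = 0.05, power 80%, 4 groups, 5 measurements. Not stated, so software defaults assumed: correlation ρ = 0.5 and sphericity ε = 1.

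- λ = f² × N × m / (1 − ρ) = 0.0225 × 80 × 5 / 0.5 = 18
- df = 3 × 4 = 12 and 76 × 4 = 304
- Power = 0.802, so 20 per arm reproduces. No covariate enters this calculation.

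**2. How often type is uneven.** The share with chronic headache, p, is not given; 10–50% is assumed. The SD of the difference in share between two arms is √(2p(1 − p)/n). For p = 0.3 and n = 24 it is √(0.42/24) = 0.132. Probabilities of a gap of at least 20 percentage points come from 200,000 simulated allocations with independent binomial counts in four arms.

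| Chronic (assumed) | SD, n = 24 | Given pair, n = 24 | Some pair, n = 24 | Given pair, n = 20 | Some pair, n = 20 |
|---|---|---|---|---|---|
| 10% | 8.7 points | 3% | 12% | 6% | 23% |
| 20% | 11.5 | 10% | 36% | 16% | 50% |
| 30% | 13.2 | 16% | 49% | 23% | 62% |
| 40% | 14.1 | 18% | 54% | 26% | 67% |
| 50% | 14.4 | 19% | 56% | 27% | 68% |

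Part of the contrast between 24 and 20 is discreteness: the threshold is met at 5/24 (20.8 points) but at 4/20 (20.0 points).

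**3. What reaches the primary comparison.** A stable difference in pain level between types cancels in the within-patient change. Only imbalance × g carries over, where g is the difference in change between types in SDs of the change score. The article gives no g; 0 to 0.8 is assumed.

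- Shift from a 20-point gap: 0.2 × g = 0, 0.04, 0.10 and 0.16 SD at g = 0, 0.2, 0.5 and 0.8.
- Standard error of a pairwise contrast: √(2/24) = 0.29 SD, or √(2/20) = 0.32 SD.

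**4. Adjusting the change score for type alone.** Simulated at 20 per arm, 30% chronic, arm effects 0/0.5/0.5/1.0 SD (all but the arm size assumed).

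| g | Type I error, unadjusted / adjusted | Power, unadjusted / adjusted |
|---|---|---|
| 0 | 0.050 / 0.050 | 0.73 / 0.72 |
| 0.5 | 0.049 / 0.049 | 0.72 / 0.73 |
| 0.8 | 0.050 / 0.050 | 0.67 / 0.73 |

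**5. Adding T1 pain by ANCOVA.** With equal SDs at T1 and T3 and correlation r, the change score has variance 2(1 − r) and the ANCOVA residual 1 − r², in units of the pain variance. The ratio is (1 + r)/2 = 0.65, 0.75 and 0.85 at r = 0.3, 0.5 and 0.7.

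- In the scenario of step 4 with g = 0, λ = 20 × (0.25 + 0 + 0 + 0.25) = 10 for the change score, giving power of about 0.74.
- Dividing by the ratio gives λ = 15.4, 13.3 and 11.8, and power of about 0.91, 0.86 and 0.81.
- Simulation, which allows for chance covariate imbalance, gives a gain of about 6 to 19 points over r = 0.3–0.7 and g = 0–0.5.

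**6. Where the covariate must enter.** In a repeated-measures ANOVA with complete data, a time-constant covariate entered as a main effect is a between-patient term. Refitting simulated five-measurement data with and without it left the time × intervention F statistic unchanged. Only covariate × time terms altered it.

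**The case against.** The strongest objection is that this rests on silence. The article never says that allocation is unstratified or the model unadjusted, and a condensed article may leave both to a fuller plan. That stands for stratification: a reader might infer that the lists were definitely not stratified, and the text does not establish it. It stands only in part for the model. The article does state a primary test and which variables are compared at baseline, and a better method than the one stated can be named.

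A reader might also infer that an imbalance in type passes straight into the primary result and biases it. The documents do not support that. The endpoint is a within-patient change, chance imbalance after randomisation is not bias, and step 4 shows the 5% level intact. Headache frequency, which type most directly reflects, is a secondary outcome, and nothing in the article shows that change in pain intensity differs by type.

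Two further objections are fair. The chronic share may be below 30%: patients using headache medication on more than 10 days a month are excluded, and recruitment is by media notices and among staff and students. At 10% chronic, the chance of a 20-point gap somewhere among four arms of 24 falls to 12%. And with multiple imputation planned, 24 per arm may be the more relevant column. Finally, outcome characteristics are compared at baseline, so a marked type imbalance might show indirectly through headache days. It would be noticed, but not corrected.

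**Conclusion.** The point holds as one of precision and interpretability. The stated primary analysis leaves unused two variables already collected, T1 pain as a covariate and headache type, in arms of 20 to 24.

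The larger cost is from T1 pain: the combined adjustment gains about 6 to 19 power points, assuming a T1–T3 correlation of 0.3–0.7, equal SDs and the arm effects above. This is measured against an unadjusted T1–T3 change score, not against the five-measurement interaction test. Type alone changes power by about −1 to +6 points over g = 0 to 0.8. Its further value is that a visible imbalance, quite likely if 20–50% are chronic, would be dealt with by a rule fixed in advance. At g = 0.5 a 20-point gap moves a contrast by 0.10 SD, about a third of its standard error. This is a modest improvement that should be made, not a flaw that invalidates the design.

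**What to change.** Under Statistical analysis, make the primary T1–T3 comparison an ANCOVA of T3 pain on arm, with T1 pain and headache type (frequent episodic or chronic, as diagnosed at screening) as prespecified covariates. Fix this before outcomes are examined by arm.

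If the repeated-measures model is kept, enter each covariate with its interaction with time, since a main effect alone does nothing for the time × intervention test. T1 pain cannot be both a repeated outcome and a covariate. If it becomes a covariate it leaves the outcome vector, and the question becomes the arm contrast at T3.

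Leave randomisation as it is; Trial status reports recruitment complete. No new data are needed. The ANCOVA costs 2 degrees of freedom. Time interactions cost more: 4 per covariate with five measurements. If type is unrelated to change, its term costs at most about one power point.
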